#### 2.4.4. Data Analyses

Descriptive characteristics of our study sample will be calculated as means ± standard deviations, frequencies, chi-square contingency analyses, and standardized residuals, unless otherwise noted. Changes in food-waste prevention behaviors, discards, motivation, opportunity ability, potential economic and nutrition-related savings, and DIEM score will be analyzed as continuous or categorical variables. Mixed factorial analyses of covariance (ANCOVA) with repeated measures will be used to determine whether mean differences exist in participant satisfaction, engagement, comprehension, changes in knowledge and planned behaviors, and food-waste variables based on socio-demographic (age, race and ethnicity, marital status, education, and income) and household-related characteristics measured at baseline. Differences will be estimated for all categorical variables using McNemar’s exact significance probability testing for paired nominal data. All quantitative statistical analyses will be accomplished using IBM SPSS Statistics. As the purpose of proof-of-concept studies is to determine whether the intervention merits more costly testing using a randomized controlled trial design, small sample sizes are acceptable because clinical, not statistical, benefit is sought.

For qualitative data, the interviews will be analyzed using content analysis based on a deductive–inductive approach. First, interview segments related to the drivers of food-waste prevention (motivation, opportunity, and ability) will be identified. For each driver, themes will be identified inductively. 

In this study, once the quantitative and qualitative data are analyzed separately, the data will then be merged together to have a greater understanding of the effects of the intervention. This will allow discongruence and congruence between both sets of data to emerge. We will report the mixed methods results with joint displays.

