### 2.4. Community Intervention

#### 2.4.1. Overview

All eight modules of the CHEF-WPM intervention will be presented in sequence over an eight-week period, facilitated by a chef–instructor with assistance from culinary students. The course will include synchronous discussions and group viewing of the CHEF-WPM video series hosted on Kajabi. Evaluation of the remote community-based intervention will use a mixed methods evaluation study design. The objectives of this mixed methods evaluation are to assess (1) intervention implementation (fidelity), satisfaction, engagement, and comprehension; (2) intervention outcomes (motivation, opportunity, ability, and household food waste); and (3) exploratory outcome (sustainable dietary behaviors). A maximum of 60 participants will be recruited in partnership with local community organizations for quantitative data-collection activities. Quantitative data collection will occur pre- and post-8-week intervention and at 6 months follow-up. A purposive sample of 20 participants will be recruited to participate in in-depth interviews at 8 weeks post-intervention. Food waste will be measured via self-report methods among the participants (*n* = 60) at pre- and post-intervention and 6-month follow-up.

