#### 2.4.2. Study Population and Recruitment

Potential participants will be 18 years or older, responsible for at least half of their household food preparation, prepare meals at home at least twice each week, have access to the internet, and understand English. The following groups will be excluded: adults unable to consent, individuals who are not yet adults (infants, children, and teenagers), and prisoners. Individuals who express interest in participating in the 8-week CHEF-WMP program will be screened for eligibility via telephone or a brief Qualtrics survey.

A convenience sample of 60 participants will be recruited for the community-level intervention, drawn primarily from a lower-income population in Philadelphia (3 cohorts of 20 individuals per cohort). This population includes a higher percentage of Black, Indigenous, and people of color than the US population. For the qualitative evaluation (in-depth interviews), a purposive sample (*n* = 20) of intervention participants will be recruited. Purposive sampling helps ensure sample diversity across age, income, educational attainment, household size, and baseline pre-disposition for food waste prevention. Participants will be recruited through university networks and in partnership with community organizations. Participants will be recruited via phone calls and/or email, digital and paper advertisements, and QR codes. These organizations together generally attract participants reflecting the city’s diverse urban demographics, namely 44% Black, 13% Latino, 7% Asian; 46,000 median household income; and 20% poverty rate.

QR codes and email links will direct individuals to a Qualtrics screening questionnaire. If they qualify, they will proceed to a study information sheet that describes participation in detail. If they are still interested after learning more about participation, they will be asked to submit their contact information and a research assistant will contact them with further details about participation. Participants will be compensated a total of USD 150 for completing the evaluation activities (quantitative measures) and an additional USD 40 for completing an interview.

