### 2.5. Withdrawal

The study team does not anticipate circumstances under which participants would need to be withdrawn from the research without their consent. Participants may elect to leave the study at any time with no penalty. If a withdrawn participant completed the study survey, their data may still be included in our analysis. Additionally, if participants withdraw from the study before the end of data collection, they will not be compensated.

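### Community Intervention: the named repeated-measures ANCOVA, if run as one three-wave model, drops households without a 6-month diary from the pre/post food-waste contrast

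*Protocol article*

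**What the plan says.** Section 2.4.4 (Community Intervention, Data Analyses) names the method: "Mixed factorial analyses of covariance (ANCOVA) with repeated measures will be used". The outcomes listed for it cover process measures and what participants know and plan to do. Household waste is listed too, and the plan words that part and the comparison to be made as follows: "food-waste variables based on socio-demographic (age, race and ethnicity, marital status, education, and income) and household-related characteristics measured at baseline". The software is fixed ("All quantitative statistical analyses will be accomplished using IBM SPSS Statistics") but the procedure within it is not.

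On timing, section 2.4.1 says: "Quantitative data collection will occur pre- and post-8-week intervention and at 6 months follow-up". The same section puts the self-reported food-waste measurement at those three points. On size, it says "A maximum of 60 participants will be recruited", and section 2.4.2 gives the make-up as "3 cohorts of 20 individuals per cohort". No dropout rate, power or detectable effect is given for this study.

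On incomplete participation, section 2.5 says: "If a withdrawn participant completed the study survey, their data may still be included in our analysis".

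**The concern.** A mixed factorial ANCOVA is a between-by-within design analysis. Despite the word *mixed*, it is not a mixed-effects model. In its usual form (in SPSS, the GLM Repeated Measures procedure) each participant contributes one row holding all levels of the within-person factor, and a row with any level missing is deleted.

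With time as a three-level factor, a missing 6-month diary removes the household from every contrast in the model. That includes the pre/post change, for which its data are complete, and any comparison of that change between baseline subgroups. Two things are at stake:

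- **Precision.** Valid pre/post pairs are discarded from a study of at most 60, whatever the reason for the missing wave.
- **Possible bias.** If returning at 6 months is related to the change already seen at post, the retained households are a selected group, and their pre/post change is not that of all households measured at both times.

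The diary asks a household to weigh, describe and classify everything it discards for a week, three times over about eight months, so some missing 6-month diaries are likely. Section 2.5 also fits awkwardly: it allows a withdrawn participant's data to be used, but a complete-record model would discard them where a later wave is missing.

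**Working it through.** **Figure to reproduce.** There is none. The community sample size comes without alpha, power, SD or dropout. The one arithmetic check, 3 × 20 = 60, agrees.

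**Inputs from the article.** N = 60 at most; three waves; single arm.

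**Assumed inputs (none are in the article).** Outcome SD 1 at each wave; correlation 0.5 between waves; retention as shown at each step; two-sided 5% and 80% power for the detectable change; true pre/post change −0.40 SD for the bias check.

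**Step 1: standard error of the pre/post change.** The variance of one change is 2(1 − 0.5) = 1, so SE = 1/√n in SD units, where n is the number of pairs used.

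Retention of 90% at post and 75% of those at 6 months:
- All pre/post pairs: 60 × 0.90 = 54, SE = 1/√54 = 0.136.
- Complete three-wave records: 54 × 0.75 = 40.5, SE = 1/√40.5 = 0.157.
- Ratio: √(54/40.5) = 1.155, about 15% larger.

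**Step 2: range of retention.** Everyone measured at post, so 60 pairs exist. The SE ratio is √(60/complete). The minimum detectable standardized paired change is from the noncentral t distribution; with all 60 pairs it is 0.37.

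| Missing at 6 months | Complete records | SE ratio | Detectable change |
|---|---|---|---|
| 10% | 54 | 1.05 | 0.39 |
| 20% | 48 | 1.12 | 0.41 |
| 30% | 42 | 1.20 | 0.44 |
| 40% | 36 | 1.29 | 0.48 |

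If 10% are already missing at post (54 pairs), the extra loss from deletion is 0%, 6%, 13% and 22% for the same four rows. The ratio does not depend on the correlation.

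**Step 3: possible bias.** 200,000 simulated records, true pre/post change −0.40 SD, 30% missing at 6 months. Dropout is either unrelated to the pre/post change or related to it by an odds ratio (OR) per SD of change. Complete-record estimates:

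| Who misses 6 months | OR 1.5 | OR 2 |
|---|---|---|
| Weaker responders | −0.52 | −0.59 |
| Stronger responders | −0.28 | −0.21 |

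With unrelated dropout the estimate is −0.40, that is, no bias.

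**Step 4: does a mixed model repair this?** 400 simulated trials of N = 60, all measured at post, about 30% missing at 6 months. Complete records are compared with a REML random-intercept model on all waves observed.
- Unrelated dropout: complete records −0.398 (mean SE 0.154); mixed model −0.400 (mean SE 0.129).
- Weaker responders more likely to miss 6 months (OR 2): complete records −0.594; mixed model −0.392.

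In step 4 dropout depends only on observed pre and post values, which is the condition under which the mixed model is valid. It was not tested against dropout that depends on the unseen 6-month value.

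**The case against.** The strongest reply is that deletion is inferred, not stated. The article names no SPSS procedure, states no complete-record rule, and does not say that all three waves enter one model. A separate pre/post model, or the MIXED procedure, would keep these households, and a condensed article may leave such detail to an analysis plan. This makes the point conditional but does not remove it: the article does fix a method, and that method's standard form has this property.

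The ANCOVA is also stated as a test of differences by baseline characteristics, not as the estimator of overall change. Of its outcomes, food waste is the one clearly measured at all three waves. McNemar tests are pairwise, so a pre/post McNemar test is unaffected. These points stand and limit the reach, although subgroup differences in change lose the same households.

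Retention may be good. Community participants receive USD 150 for the quantitative measures, and section 2.5 withholds payment from those who withdraw before data collection ends. The article also describes a proof of concept in which "small sample sizes are acceptable because clinical, not statistical, benefit is sought". That lowers the stakes, but it is no reason to discard valid pairs from a small sample.

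Two stronger readings are tempting and not supported:
- A reader might infer that the best responders will define the effect. The article gives neither a dropout rate nor its direction, and step 3 shows that the bias can be absent or reversed.
- A reader might extend the point to the 3- and 6-month data of Population Intervention 2, because section 2.3.4 uses the same words. There the ANCOVA is stated only for satisfaction, engagement and comprehension, which are asked after each embedded video. Motivation, opportunity and ability, the main content of the 3- and 6-month surveys, have no named model. Complete-record figures for that study would describe an analysis that the article does not state.

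**Conclusion.** The point holds for the Community Intervention in conditional form. If the named ANCOVA is run in its standard form with all three waves in one model, households missing only the 6-month diary leave the pre/post food-waste contrast as well. The loss of precision then follows whatever the cause of dropout: about 15% in the standard error under 90% and 75% retention, and 5% to 29% across the range in step 2. Bias is a possibility whose size and sign the article gives no basis to fix. Every retention, correlation and effect value used is an assumption. The loss is moderate, but it is avoidable at almost no cost, so the change is worth making.

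**What to change.** In section 2.4.4, for outcomes measured at several waves, replace the repeated-measures ANCOVA with a linear mixed model for repeated measures (SPSS MIXED). Use time as a categorical factor, an unstructured covariance (three variances and three covariances for three waves) and baseline covariates. Where differences by a baseline characteristic are tested, add its interaction with time. State that all observed records are used.

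In section 2.5, change *may* to *will* for the inclusion of data collected before withdrawal, so that inclusion is not left to judgement.

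The cost is wording only; the software and the data collection stay as they are. The downside is reliance on missing at random, which the data cannot confirm. Add one simple sensitivity analysis, for example repeating the 6-month estimate with the missing values shifted by a stated range in either direction. Section 2.3.4 needs no change on this account.

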#### 2.4.5. Community Advisory Board

A community advisory board has been recruited from our community partners to provide input into the design, content, guest-chef representation, and recipes of the videos. The advisory board will meet quarterly via Zoom and in-person (hybrid model), and each member will be paid an incentive for their participation.

### 2.5. Withdrawal

The study team does not anticipate circumstances under which participants would need to be withdrawn from the research without their consent. Participants may elect to leave the study at any time with no penalty. If a withdrawn participant completed the study survey, their data may still be included in our analysis. Additionally, if participants withdraw from the study before the end of data collection, they will not be compensated.

## 3. Potential Benefits and Risks of Study Participation

As with any study involving the collection of data, there is a risk of harm resulting from a breach of privacy and/or confidentiality. If information linking participants to their responses is inadvertently disclosed, we do not anticipate any significant harm to result to participants. However, we will still secure the information we collect (as outlined in the data-protection section) to minimize the probability of this risk. We will also maintain feedback and discussion data in separate folders without individual identifiers. Once the research study is complete and individually identifiable information is no longer necessary, the key linking individuals to their responses will be destroyed, further reducing the magnitude of this risk.

During the interviews, it is possible that some activities or questions will lead to momentary embarrassment, discomfort, or unease. The probability and magnitude of discomfort are not expected to be greater than participants would ordinarily encounter in their everyday lives and will be disclosed during the informed consent process. We do not anticipate any costs to participants for taking part in this study. We do not expect any of our procedures will carry unforeseen risks to participants or individuals not participating in the research.

There may be no direct benefit to participants of this research study, though they may value the opportunity to participate in the class. The information collected may benefit society by developing a novel intervention to enhance participants’ motivation, opportunity, and ability to reduce consumer food waste. There are minimal risks associated with this study. The probability and magnitude of discomfort are not expected to be greater than participants would ordinarily encounter in their everyday lives and will be disclosed during the informed consent process. The study procedures, particularly the food-waste tracking, require an investment of time and effort.

## 4. Data Monitoring

The principal investigators will monitor and review the study progress, participant safety, and the accuracy and security of the emerging data. All information collected in this study will be kept confidential as required by law. Names will not be attached to the study participants and a master list, and the data elements and survey responses will be kept in a secure and encrypted database, which can only be accessed by research team members. Due to the low-risk nature of the intervention, a Data and Safety Monitoring Board has not been formally established. All adverse events will be reported to the principal investigators and reviewed by the study team to determine whether the study should be discontinued due to participant safety. Quality assurance procedures will be implemented, including rigorous attention to manual data cleaning, generation of monthly query reports, and ranges and data validation checks.

## 5. Ethics and Dissemination

### 5.1. Consent

The consent process for each of the three types of evaluations will be the same. The participants will complete a screening questionnaire to determine study eligibility. If eligible, they will be directed to a study information sheet for exempt research. After reading the information sheet for exempt research, proceeding to the survey will serve as a proxy for informed consent. In the information sheet, the research team’s contact information will be provided to the participant. Participants are encouraged to contact the research team if there are any questions and will be given the opportunity to discuss the study with their surrogates or think about it prior to agreeing to participate. They may withdraw consent at any time throughout the study. A copy of the information sheet will be emailed to participants for their records.

### 5.2. Confidentiality

Participant confidentiality is strictly held in trust by the investigators, study staff, and the sponsor and their agents. The study protocol, documentation, data, and all other information generated will be held in strict confidence. No information concerning the study or the data will be released to any unauthorized third party without prior written approval of the sponsor. The study monitor or other authorized representatives of the sponsor may inspect all study documents and records required to be maintained by the investigator. 

Confidentiality will be protected by including only information needed to assess study outcomes, minimizing to the fullest extent possible the collection of any information that could directly identify participants, and maintaining all study information in a secure manner. To ensure participant privacy and confidentiality, a unique study identifier will be assigned to each participant. The data and records will be kept locked and secured, with any computer data password protected. Protected health information (PHI) will not be collected in this study. Therefore, we are requesting a waiver of HIPAA authorization. To ensure privacy, all interviews will be conducted via HIPAA-compliant Zoom technologies. Links to Qualtrics surveys will be encrypted. To protect the confidentiality of participant responses, the data will be de-identified and unique identification numbers will be assigned to participants.

### 5.3. Dissemination

We will disseminate the study findings through conference presentations and publications in peer-reviewed international journals. Only aggregate data without individually identifiable information will be published. As this study is a feasibility study, the results will be used to inform and develop a larger, adequately powered, randomized controlled trial, if appropriate.

## 6. Results

This research investigates a highly scalable solution to strengthen consumers’ motivation, opportunity, and ability to reduce food waste at the locus where most wasted food occurs by adapting professional culinary education interventions to the home kitchen. This interdisciplinary project combines knowledge from the fields of culinary arts and science, education, consumer behavior, nutrition, environmental science, and public health to provide low-friction interventions and flexible access to content that will resonate with consumers. Rather than teaching home cooks through an overbearing and expensive didactic approach, this intervention empowers home cooks to prevent and minimize food waste in a way that is convenient, accessible, culturally appropriate, and scalable. This intervention offers home cooks the opportunity for professional-level culinary education in a way that saves money, utilizes cultural flavors, provides nutrition background information, and builds confidence, all while reducing food waste.

This research also includes multiple innovative features, addressing critical research gaps and pioneering new approaches:*Cooks as consumer educators*, reflecting the NAS report highlighting the need to use such influencers [4];*Bite-size videos*, adapting food waste education to a social media-friendly modality that many people use to learn about cooking today. This allows us to create or support new or existing influencers, whose reach and appeal are hard to match through more traditional research interventions;*Innovative application and assessment* of motivation, opportunity, and ability (MOA) metrics [11];*Innovation in a longer timeframe of follow-up* and in comparing and contrasting the same intervention in both community and population settings;*Direct measurement of waste*.

## 7. Discussion

Wasted food is the largest component of the landfill and incineration stream [3], and most of the waste generated remains at the consumer level [2]. Hence, the purpose of this research protocol is to evaluate the feasibility, acceptability, and preliminary efficacy of a household food-waste prevention and minimization intervention, which consists of a culinary education video series for home cooks. The specific aims of this protocol are to (1) assess the effects of the intervention at a population level across process (feasibility, usage, acceptability, and satisfaction) and preliminary efficacy (motivation, opportunity, and ability) metrics and (2) assess the effects of the intervention at a community level across process (feasibility, usage, acceptability, and satisfaction) and preliminary efficacy and exploratory (motivation, opportunity, ability, household food waste, and sustainable dietary practices) metrics.

The evaluation seeks to understand intervention effects both when accessed voluntarily in a population-based setting, and via a more intensive delivery as part of a program in a community setting. Findings from the two distinct evaluation studies will be jointly discussed and triangulated to support larger conclusions about the intervention’s desirability, impact on motivation, opportunity, ability, and food waste, and the potential directions for further improvement. The intervention’s benefits may be both short and long term because the skills and attitudes presented can shape ongoing kitchen practices and norms.

